### 2.2. Study Sample

To assess the efficacy of an MTM-based intervention aimed at promoting responsible gambling among college students, participants will be recruited from the student population of a southwestern university. This sampling approach was chosen for its accessibility and the notable prevalence of gambling behaviors within this demographic [16]. Given that the legal gambling age in the United States is typically 21 [17], the eligibility criteria for this study will include the following:Enrollment as a student at the southwestern college.Age 21 or older.Proficiency in English.A score of 3 or higher on the PGSI [14].Consent to participate in this study.

Students currently undergoing treatment for gambling issues will be excluded to prevent potential confounding effects associated with concurrent interventions.

The Problem Gambling Severity Index (PGSI), a standardized tool for assessing gambling-related risk behaviors [14], will be used to screen the participants. Individuals scoring between 3 and 7 on the PGSI are classified as moderate-risk gamblers, indicating behaviors such as exceeding gambling budgets, losing track of time, or experiencing guilt over gambling [14]. A score of 8 or higher designates an individual as a problem gambler, reflecting significant gambling-related issues [14]. Therefore, students scoring 3 or above on the PGSI who meet all other eligibility criteria will be included in this study.

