### 2.4. Study Procedure

Participant recruitment will target college students aged 21 and older at the university. The recruitment efforts will include email invitations that introduce this study and invite eligible students to participate. The intervention sessions will be conducted in person. The participants will be randomly assigned to either the experimental group (RESPONSIBLEPLAY^©^: MTM-based intervention) or the comparison group (knowledge-based intervention) using SAS PROC SURVEYSELECT. Participant data will first be imported from an Excel file, and each participant will be assigned a unique ID. Simple random sampling (SRS) will then be conducted using PROC SURVEYSELECT, ensuring equal probability of assignment to either group. A fixed seed (12345) will be used to ensure reproducibility. The function will generate a selection indicator (Selected = 1 for the experimental group and Selected = 0 for the comparison group), which will be used to assign the participants accordingly. The final randomized dataset, including group assignments, will then be exported for implementation.

The intervention will be conducted over three weeks, with one session scheduled per week. Each session will span three days, offering multiple time slots to accommodate the participants’ schedules. This approach ensures that all the participants receive the same intervention content while allowing flexibility in attendance. The first session (Week 1) will include an orientation, completion of the pre-intervention survey, and the start of the intervention activities. The final session (Week 3) will consist of intervention activities followed by the post-intervention survey.

To enhance attendance and engagement, the participants will receive email reminders before each session. Additional reminders will be sent to the experimental group between sessions and after the intervention to reinforce the practice of responsible gambling behaviors. At the eight-week follow-up, the participants will attend a final assessment session, which will be scheduled in advance. Email reminders will also be sent to maximize participation.

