### 2.6. Strategies to Prevent Cross-Group Influence

To minimize cross-group influence, this study will implement several strategies. Intervention sessions for the experimental and comparison groups will be scheduled separately, and group-specific materials will be clearly labeled and distributed exclusively to each group. The participants will be briefed on confidentiality and instructed not to discuss session content with members of the other group. The research team will actively monitor sessions to ensure adherence to these protocols and address any issues promptly. These measures aim to preserve this study’s integrity and validity.

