### 2.9. Instrumentation

The survey tool for this research consists of a 54-item questionnaire (Supplement S4) specifically designed and refined through a meticulous two-stage review process conducted by a panel of six experts. These specialists, with expertise in MTM theory, instrumentation, and the target population, evaluated the questionnaire’s face and content validity in two rounds. They assessed the clarity, readability, and relevance of the items, leading to wording adjustments and the removal of one item from the behavioral confidence section. Following these revisions, the panel reached a unanimous agreement on the adequacy of the content and face validity for each MTM subscale. The finalized instrument achieved a Flesch Reading Ease score of 57.4 and a Flesch–Kincaid Grade Level of 8.7, confirming its suitability for the intended audience. In prior studies utilizing this MTM-based instrument among college populations, internal consistency estimates (Cronbach’s alpha) for the subscales ranged from 0.76 to 0.89, indicating acceptable to strong reliability [11].

Participants in this study must complete the 54-item survey based on the Multi-theory Model (MTM) at three time points: before the intervention (pre-test), immediately after the intervention (post-test), and during the follow-up period at eight weeks post-intervention. Prior to participation, all individuals will be required to provide informed consent by signing a consent form. This ensures that the participants understand the purpose of this study, their role, and their rights, including confidentiality and voluntary participation.

The initial questions of the survey focus on the frequency and types of gambling activities the participants had engaged in over the past 30 days. These questions are essential for establishing baseline measurements and serve as screening criteria for this study. The participants are asked to report the number of days they gambled during this period and to specify the types of gambling activities they participated in, such as lotteries, sports betting, poker, and online gambling. This information helps to categorize the participants based on their gambling behavior and ensures that the sample includes individuals who are actively engaged in gambling.

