After the baseline questions, the survey includes the Problem Gambling Severity Index (PGSI) to assess the impact of gambling on various aspects of the participants’ lives over the past 12 months. This section consists of nine questions designed to evaluate the severity of gambling-related issues by examining factors such as financial strain, emotional distress, health complications, and social consequences linked to gambling behaviors. The participants rate their experiences on a scale from 0 (“Never”) to 3 (“Almost always”), providing a detailed measure of the extent to which gambling has affected their lives. This information helps classify participants as low-risk, moderate-risk, or problem gamblers based on their responses. The Problem Gambling Severity Index (PGSI) is a widely used and validated measure of gambling-related risk and severity. As a part of the Canadian Problem Gambling Index, it is commonly used in both general and college populations. The PGSI has demonstrated strong internal consistency in previous studies, with reported Cronbach’s alpha values typically ranging from 0.84 to 0.91, supporting its reliability as a measure of gambling-related risk behaviors [20].

The third section of the survey consists of 32 questions aimed at assessing the constructs of the Multi-theory Model (MTM) for both the initiation and sustenance of behavior change. These questions explore the participants’ readiness to initiate responsible gambling behaviors and the strategies they employ to maintain these behaviors over time. By focusing on the psychological, social, and environmental factors that influence behavior change, this section provides valuable insights into participants’ motivation, confidence, and commitment to adopting and sustaining responsible gambling practices. The final section of the survey collects demographic information, such as age, gender, and educational background, ensuring a thorough understanding of the participant population and enabling more accurate data analysis.

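### The pre-test that serves as baseline is taken after allocation, in separately scheduled arm sessions, and the screening role given to its opening items conflicts with that timing

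*Protocol article*

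**What the plan says.** **Order of events.** Section 2.4 describes import of a participant list, allocation with PROC SURVEYSELECT, and then: "The final randomized dataset, including group assignments, will then be exported for implementation". The next paragraph turns to the sessions: "The first session (Week 1) will include an orientation, completion of the pre-intervention survey, and the start of the intervention activities".

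**Separation of arms.** Section 2.6: "Intervention sessions for the experimental and comparison groups will be scheduled separately". Materials are labelled and handed out by group.

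**Screening.** Section 2.2 lists, among the eligibility criteria, "A score of 3 or higher on the PGSI", and says that the PGSI "will be used to screen the participants". It does not say when. Section 2.9 says of the survey's opening items, on gambling in the past 30 days: "These questions are essential for establishing baseline measurements and serve as screening criteria for this study". The nine PGSI items follow in the same 54-item survey. That section names three administrations (pre-test, post-test, eight-week follow-up) and no separate screening one.

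**Use of the pre-test.** It is one of three time points in the mixed ANOVA and the source of the ANCOVA trigger (Section 2.13). It also feeds the between-arm t-tests at pre-test (Section 2.12).

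**The concern.** A baseline should be fixed before anyone can know or react to the assignment. Here the survey is answered inside a session that belongs to one arm, and it is listed after an orientation. Its 32 Multi-theory Model items ask about readiness, motivation and confidence. Such self-reports can move with what a participant has been told or believes about the group. Section 2.1 calls the trial single-blinded but does not say who is blinded.

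Three things are at stake:

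- An arm difference arising at the pre-test enters the group-by-time contrast directly. It can mimic or mask an effect, depending on its direction.
- Anyone assigned who does not attend Week 1 has no pre-test. Section 3.2 offers a baseline comparison of completers and non-completers as its safeguard against selective retention, and that comparison cannot include these people. Such losses could differ by arm: as Section 2.7 reads, the experimental group receives a gift card after each session and at follow-up, while for the comparison group only one at the end of follow-up is described.
- If the 30-day items really screen at the first administration, people could be excluded after assignment.

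**Working it through.** **1. Is the pre-test after allocation?** Section 2.4 puts assignment and export before the description of the sessions. That order alone might be only narrative. Section 2.6 settles it: separate sessions can be scheduled only if each person's arm is known. The pre-test falls in the first of those sessions, so it follows allocation. It is listed before the intervention activities start, so no intervention activity precedes it.

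**2. Does the screening wording fit?**

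| Place | What it implies |
|---|---|
| 2.2 | PGSI of 3 or more required; the PGSI is used to screen; timing not given; no 30-day criterion listed |
| 2.4 | Invitations go to students described as eligible; pre-test in Week 1, after assignment |
| 2.9 | 30-day items of the survey screen; first of three administrations is the pre-test |

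Sections 2.9 and 2.4 together put a screening item after randomisation. Sections 2.9 and 2.2 disagree on whether recent gambling is a criterion at all. Neither shows when the PGSI screen takes place.

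**3. What could a pre-test shift do?** The plan gives no figure to reproduce here, so this is an illustration only. From Section 2.3: m = 3 time points, correlation 0.5, sphericity correction 1, alpha 0.05, N = 60 (40 × 1.5). Assumed, not in the document: an arm difference of d SD at pre-test, none at the later visits, and equal SDs and group sizes.

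- Centred arm differences: (2d/3, −d/3, −d/3). Each arm carries half of each.
- f² = (1/4) × (4/9 + 1/9 + 1/9)/3 × d² = d²/18.
- Noncentrality: λ = f² × N × m/(1 − 0.5). Degrees of freedom: 2 and 2(N − 2).
- For d = 0.2: f² = 0.04/18 = 0.00222. At N = 60, λ = 0.00222 × 60 × 3/0.5 = 0.80 with df 2 and 116, and the rejection rate is 0.113. At N = 40, λ = 0.53 with df 2 and 76, and the rate is 0.091.

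| Assumed d (SD) | N = 60 | N = 40 |
|---|---|---|
| 0 | 0.050 | 0.050 |
| 0.1 | 0.065 | 0.060 |
| 0.2 | 0.113 | 0.091 |
| 0.3 | 0.202 | 0.147 |
| 0.5 | 0.493 | 0.341 |

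On the effect scale, with a slope of 0.5, a 0.2 SD shift moves a baseline-adjusted difference by 0.5 × 0.2 = 0.1 SD and a change-score difference by the full 0.2 SD.

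**The case against.** The best defence is that the order of screening is natural and merely condensed. Section 2.2 screens on the PGSI, Section 2.4 invites eligible students and then randomises participants, and the flow diagram and design figure are not available here. A reader might infer that eligibility as a whole is decided after randomisation. The document does not support that: no section places the PGSI check in Week 1 or plans exclusions there. This part of the defence stands. What remains is that the 30-day wording conflicts with the timing and with Section 2.2, though that list is not worded as exhaustive and no 30-day threshold is given.

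No section says that orientation differs by arm, so arm-specific content is a possibility only. The PGSI (past 12 months) and the gambling items (past 30 days) are also less open to a brief orientation than the attitudinal items are. Both points stand and narrow the risk mainly to the Multi-theory Model scores.

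A reader might also infer that Week 1 non-attenders would go uncounted. Section 3.2 contradicts this, since attrition is to be reported for each phase. Section 2.11 settles on a per-protocol analysis alone, so these people would be left out of the outcome analysis whenever the pre-test was given. An earlier survey would not bring them back; it would let the completer comparison include them.

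None of this alters the fact that the pre-test follows allocation.

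**Conclusion.** The point holds in a limited form. That the baseline is collected after allocation, in arm-specific sessions, follows from Sections 2.4 and 2.6 without any assumption. That the stated screening role of the 30-day items conflicts with this timing and with the eligibility list also follows from the text. Eligibility decided after randomisation remains an open risk until the timing of the PGSI check is stated.

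Neither the size nor the direction of bias can be derived from the document. The rise from 0.05 to about 0.11 at N = 60 rests wholly on the assumed 0.2 SD shift; at 0.1 SD the rate would be 0.065. The case for changing the plan is that a route to bias can be closed at little cost, not that bias has been shown.

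**What to change.** - Give the 54-item pre-test after consent and the PGSI eligibility check, but before PROC SURVEYSELECT is run, and use it as the baseline in every analysis.
- State when the PGSI eligibility check takes place.
- Reconcile the screening wording in Section 2.9 with Section 2.2: either list recent gambling as a criterion, checked before assignment, or describe those items as baseline description only.
- Make no eligibility exclusions after assignment.
- Section 2.5 says that the study is underway. Where allocation has already taken place, report the actual order of events and, by arm, the losses between allocation and pre-test.

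**Cost.** It is the same instrument given earlier, with no change to the planned sample size. The baseline would precede Session 1 by days to weeks. If one administration serves as both screen and baseline, selecting on a PGSI of 3 or more builds regression to the mean into the within-arm change, though not into the between-arm comparison. A separate PGSI check before the pre-test lessens this, at the price of one more short questionnaire.

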### 2.7. Interventions

The experimental group will participate in a three-week intervention based on the MTM of health behavior change [10]. This intervention includes role-playing, psychodrama, journaling, and exploring recreational alternatives to address gambling behaviors. Participants will document their gambling-related activities, physical and emotional challenges, and achievements throughout the program. Each session will last approximately 60 min and be held once per week for three weeks. To encourage participation, the participants will receive a USD 20 gift card after each session and again at the eight-week follow-up.

Session 1: This session explores the pros and cons of gambling, emphasizing how the benefits of responsible gambling outweigh its risks. The participants work on building behavioral confidence, developing plans for responsible gambling, and identifying environmental changes that support responsible gambling practices (Supplement S1).

Session 2: In this session, the participants reflect on their emotions related to gambling and explore techniques for transforming negative emotions into positive ones. They receive guidance on journaling and record-keeping as tools for self-awareness and accountability. Additionally, the participants engage in recreational activities as alternatives to gambling and identify sources of social support that encourage responsible gambling behaviors (Supplement S1).

Session 3: The final session features a guest speaker from the Nevada Council on Problem Gambling, who will provide insights and motivation. The activities focus on initiating responsible gambling behaviors over the next eight weeks and strategies for sustaining them. The participants also receive practical demonstrations of techniques to implement and maintain responsible gambling behaviors long term (Supplement S1).

The comparison group will participate in three knowledge-based sessions, each featuring lectures and presentations focused on gambling behavior (Supplement S2). Each session will last approximately 60 min. At the conclusion of the eight-week follow-up, the participants will receive an incentive (a USD 20 gift card) as a token of appreciation and to support their continued learning. The Table 2 describes the alignment of intervention components with MTM constructs and behavioral outcomes.

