Descriptive statistics (means, SDs)	Summarize continuous variables such as age and baseline MTM/PGSI scores.
Descriptive statistics (frequencies, %)	Describe categorical variables such as gender, class standing, and gambling types.
Chi-Square Test	Assess baseline equivalence in categorical variables between intervention and comparison groups.
Independent samples t-test	Assess baseline equivalence in continuous variables (e.g., PGSI, MTM scores) across groups.
Two-Way Mixed ANOVA	Evaluate within- and between-group differences in PGSI and MTM constructs over time (pre-, post-, follow-up), to assess efficacy of the MTM-based intervention.
Mixed ANCOVA (if needed)	Adjust for baseline differences in key variables (e.g., age, PGSI) when detected.

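### The post-test closes session 3, leaving gambling behaviour little time to change, yet the three-wave ANOVA gives it the same standing as the eight-week reading in judging efficacy

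*Protocol article*

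**What the plan says.** **Timing of the surveys.** Section 2.4 places the pre-test in week 1: "The first session (Week 1) will include an orientation, completion of the pre-intervention survey, and the start of the intervention activities". It places the post-test in week 3: "The final session (Week 3) will consist of intervention activities followed by the post-intervention survey". Section 2.9 gives the two later readings as "immediately after the intervention (post-test), and during the follow-up period at eight weeks post-intervention".

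**What the sessions do.** For the experimental arm, section 2.7 says of session 1: "The participants work on building behavioral confidence, developing plans for responsible gambling, and identifying environmental changes that support responsible gambling practices". Session 2 turns to emotions, journaling, recreational alternatives and social support. Session 3 has a guest speaker, partly for motivation, and then: "The activities focus on initiating responsible gambling behaviors over the next eight weeks and strategies for sustaining them". For the comparison arm the article describes lectures and presentations and mentions no such speaker.

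**What is measured.** The PGSI is used "to assess the impact of gambling on various aspects of the participants’ lives over the past 12 months" (section 2.9). The 32 MTM items cover readiness to start and also "the strategies they employ to maintain these behaviors over time".

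**How efficacy is judged.** Section 2.13 applies a two-way mixed ANOVA to PGSI and MTM scores over the three readings and names within-subject and between-group effects. Table 3 gives its purpose: "Evaluate within- and between-group differences in PGSI and MTM constructs over time (pre-, post-, follow-up), to assess efficacy". No reading or contrast has priority. Section 2.11 refers to a primary outcome measure without naming it or its time point.

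**The concern.** Session 3 directs participants towards behaviour in the eight weeks that follow, and the post-test is filled in before any of those weeks has begun. It also follows directly on a motivational component that the article describes for one arm only. What it captures best is the state of mind at the end of the course: confidence, readiness, intention. Use of maintenance strategies, and gambling behaviour itself, can have changed only as far as sessions 1 and 2 have already brought about.

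The named efficacy analysis does not reflect this difference. If the arms differ at post-test and no longer differ at eight weeks, the group-by-time test can still be significant, and Table 3 allows that result to be read as efficacy. The primary objective in section 2.10 is to promote responsible gambling behaviour, and the intervention is meant to maintain it over time. A vanished end-of-course lift would not meet that aim.

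**Working it through.** **1. Time available at each reading.** Sessions are weekly, so session 1 to session 3 is about 2 weeks and session 1 to follow-up about 2 + 8 = 10 weeks. Taking 12 months as 52 weeks:

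| Reading | PGSI window after session 1 | PGSI window after session 3 |
|---|---|---|
| Post-test | 2/52 = 4% | 0/52 = 0% |
| Follow-up | 10/52 = 19% | 8/52 = 15% |

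About 96% of the PGSI window at post-test precedes any intervention.

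**2. Inputs for the power check.** From section 2.3: two groups, three readings, correlation rho = 0.5, non-sphericity correction 1, alpha 0.05, 20 per group before and 30 per group after the attrition allowance. The article gives no effect by time point, so the between-arm difference d is an assumption, shown for 0.5, 0.75 and 1.0 SD.

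The plan's only related figure is the 20 per group. With f = 0.30 under the usual G*Power convention, the interaction noncentrality is f² × N × 3/(1 − rho). N = 20 in total gives 0.09 × 20 × 3/0.5 = 10.8 and power 0.81; N = 40 gives power 0.99. So 20 is reproduced as a total, not per group. That is a separate matter and does not affect what follows, which takes the stated group sizes as given.

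**3. Group-by-time test.** With n per arm and group differences d₁, d₂, d₃ at pre-test, post-test and follow-up, the noncentrality is λ = (n/2) × Σ(dⱼ − mean)²/(1 − rho), on 2 and 2(2n − 2) df.

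For the profiles (0, d, 0), (0, 0, d) and (0, d, d), the sum of squared deviations is (2/3)d² in every case. The test therefore has the same power for all three. For d = 0.75 and n = 20: λ = 10 × (2/3) × 0.5625/0.5 = 7.5.

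| d (SD), any of the three profiles | 20 per arm | 30 per arm |
|---|---|---|
| 0.5 | 0.34 | 0.49 |
| 0.75 | 0.67 | 0.85 |
| 1.0 | 0.90 | 0.98 |

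**4. Between-group main effect.** Here λ = (n/2) × 3 × (mean difference)²/(1 + 2 rho), on 1 and 2n − 2 df. For d = 0.75 and n = 30:
- Effect at both later readings: mean 0.50, λ = 15 × 3 × 0.25/2 = 5.625, power 0.65.
- Effect at follow-up only: mean 0.25, λ = 15 × 3 × 0.0625/2 = 1.406, power 0.22.

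**5. Eight-week comparison adjusted for pre-test.** λ = (n/2) × d²/(1 − rho²), on 1 and 2n − 3 df. For d = 0.75:
- n = 20: λ = 10 × 0.5625/0.75 = 7.5, power 0.76, against 0.67 for the three-wave test.
- n = 30: λ = 15 × 0.5625/0.75 = 11.25, power 0.91, against 0.85.

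Without baseline adjustment, the pre-to-follow-up change contrast has λ = 10 × 0.5625/[2(1 − 0.5)] = 5.625 at n = 20 and power 0.64, below the three-wave test. The gain therefore depends on baseline adjustment, not on the timing of the post-test.

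**The case against.** **A reader might infer that the post-test is taken before any effect can occur.** The article does not support this. Session 3 is the last of three. Planning and confidence work start in session 1, journaling and social support come in session 2, and section 2.4 provides reminders to the experimental group between sessions. Some behaviour change by week 3 is possible, and even an item on maintenance strategies could reflect journaling already begun. Confidence, readiness and emotional transformation can properly be measured at that moment, and section 3.2 offers the MTM scores as the short-term measure. The concern must therefore be limited to PGSI and sustenance, and to the full effect rather than any effect.

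**A reader might also infer that a null post-test weakens the group-by-time test for an effect seen only at follow-up.** It does not: power is the same as for an effect at both later readings (step 3). Only the between-group main effect is diluted.

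**The size of a transient lift is assumed.** At 0.3 SD the chance of a significant group-by-time result is only 0.15 at 20 per arm and 0.20 at 30. A large lift on a 12-month recall scale is hard to credit, so the risk of a transient positive lies mainly with the MTM scores. The three means will be available, and a careful report would show that a lift had gone.

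**Disclosure and scope.** Section 3.2 concedes that the PGSI is insensitive to short-term change and adds item-level analyses. It does not discuss the in-session reading or its equal standing. A primary time point is often left to an analysis plan, but this article does state its efficacy method and purpose, and as stated that method does not separate an immediate response from a lasting one.

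**Conclusion.** The point holds in limited form. For PGSI and the sustenance constructs, the post-test leaves little or no time for the full effect, yet it counts the same as the eight-week reading in the stated efficacy test. A post-test-only difference is as likely to give a significant group-by-time result as a lasting one of the same size: 0.34 to 0.90 at 20 per arm and 0.49 to 0.98 at 30 per arm for assumed differences of 0.5 to 1.0 SD. The between-group effect loses power when the benefit appears only at follow-up (0.22 against 0.65 at 0.75 SD and 30 per arm).

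These figures rest on rho = 0.5, sphericity and alpha 0.05 from section 2.3, on complete data, and on assumed effect sizes. The equality of the three profiles in the group-by-time test does not depend on the effect size chosen. The harm is chiefly to interpretation. The survey schedule itself is not at fault, and an immediate reading of MTM constructs is legitimate.

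**What to change.** In sections 2.10 and 2.13 and in Table 3, state that:
- efficacy on gambling behaviour (PGSI) and on the sustenance constructs is judged by the between-arm difference at eight weeks, adjusted for the pre-test score;
- the post-test is reported separately as an immediate response, chiefly for the MTM constructs;
- a post-test difference that is absent at eight weeks is not called efficacy on behaviour.

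The three-wave ANOVA can stay as a description of the course over time. Section 2.5 says the protocol is under way, so the change should be made before outcome data are examined by arm.

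**Cost:** wording and one contrast, with no added data collection and no change to the survey schedule. A short-lived effect no longer counts as success. The deciding comparison depends on follow-up attendance, although the per-protocol analysis in section 2.11 already requires completed follow-up.
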